### Transportability of Results

To assess how many young Danish people may benefit from Mindhelper, if it proves to be effective, we will compare the characteristics of our sample to a nationally representative sample of 31,420 young Danish people aged between 15 and 25 years. The national sample, drawn from the study “Young in 2023—Room for Everybody?” includes self-reported data on demographics, WHO-5, and PHQ-4 [50]. Furthermore, we will use the national sample to retrieve information on how our study population varies from a representative sample.

### Qualitative Contributions

To gain a deeper understanding of how young people use and integrate self-help tools from Mindhelper in their everyday lives to promote mental health, a qualitative interview study will be conducted. In total, 20 young people will be interviewed twice, approximately 3 months apart. Participants for the interviews are recruited from the intervention group at T3. From the pool of participants who provide consent to be contacted to participate in interviews, 20 participants will be selected, considering gender, age, region of residence, and medical history of mental health disorders, to ensure a diverse group. This information will be based on responses to the T1 survey and solely used for selection purposes without influencing the themes of the interviews.

Selected respondents will be contacted via SMS text messages to arrange a time for the first interview. After the first interview, respondents will again be contacted via SMS text messages to schedule the second interview. Upon completing both interviews, participants will receive a cinema gift card via an SMS text message. Each interview will last up to 1 hour and follow a semistructured interview guide. The interviews will be conducted by [name] via phone or Microsoft Teams or Zoom (Zoom Communications, Inc), based on the participant’s preference. The interviews will be audio recorded and transcribed verbatim. Conducting the first interview at T3 will allow for insights into how respondents experience receiving the intervention and how they have used it (eg, “What themes or tools on Mindhelper have you used?” “What did you gain from reading about these themes?” and “How has it been receiving the Mindhelper text messages?”). The second interview held after T4 will contribute to the knowledge of how respondents use Mindhelper following the SMS text message campaign’s end (eg, “Have you been on Mindhelper since you stopped receiving text messages about the website,” and “Has participating in this study changed your use of websites, apps, or social media to seek knowledge or advice about mental health?”). Themes for the first and second interviews are shown in Table 2. The qualitative data analysis software NVivo (Lumivero) will be used to process all data, with interviews analyzed according to the research questions, systematic text condensation, and template analysis [44,51].

**Table 2 table2:** Themes for the first and second interviews.

Theme	First interview	Second interview
Background: gender, age, region of residence, and primary occupation	✓	
Knowledge of Mindhelper: How did they become aware of Mindhelper?	✓	
Use of Mindhelper: Have they used Mindhelper before or during the SMS text message campaign?	✓	
How they have used Mindhelper: What topics and features have they used on Mindhelper?	✓	✓
Use of Mindhelper after SMS text message campaign ended: Future use of Mindhelper?		✓
Impact of Mindhelper: What has the impact been? Are there any areas for improvement on Mindhelper?	✓	✓
Handling mental health struggles: What challenges does the young person face? What is their behavior in response to mental health struggles?	✓	
Handling mental health struggles: Are there any changes since last time?		✓
Digital behavior: How is the internet used in relation to mental health topics? Where do they get their information?	✓	
Help seeking—online versus network: When do they use the internet, and when do they turn to friends and family or professionals?	✓	

## Results

This study was fully funded in November 2022, and the data collection started in January 2025. As of August 2025, we have enrolled 2613 people. The data analysis will start after data collection concludes, by early 2026, and the results of the primary outcome are expected to be published in the fall of 2026.

## Discussion

### Anticipated Findings

This is the first large-scale RCT to evaluate the effects of a digital, multicomponent, self-guided mental health promotion service among young people. If effective, this highly scalable service may contribute to combating the trend of rising mental health issues among young people and address key challenges in primary care by delivering timely, coordinated, and effective services to young individuals, potentially at a low cost [52].

### Strengths and Limitations

This study has several strengths, including the large sample size, which enhances statistical power, enabling the detection of even small effect sizes that, while modest at the individual level, could generate substantial impact at the population level if the service is widely scalable and accessible. In addition, this study includes a more diverse participant sample than previous research, encompassing a broader population beyond specific university settings or patients with specific clinical symptom profiles [53,54]. This diversity may more accurately reflect the potential user base for the intervention. This is the first study to assess the cost-effectiveness of a digital, self-guided mental health promotion service targeting young people.

This study also has limitations, including that Mindhelper is publicly accessible and will continue to be so during the trial, raising the risk of exposure misclassification, which could dilute any observed differences between intervention and control groups. This misclassification would likely bias results toward the null, underestimating the intervention’s effect. However, in the feasibility study, very few control group participants accessed thewebsite [18]; therefore, we do not consider this to be a major risk.

### Conclusions

Individuals most commonly access Mindhelper via diagnostic and research-related search queries through search engines (eg, Google), where users are organically drawn to the content. In contrast, the Mindhelper study actively directs content to the intervention group. Therefore, our study deviates from the natural use patterns and evaluates the combined effects of the SMS text message campaign and Mindhelper. We create a situation that brings participants to Mindhelper, but Mindhelper and the use of Mindhelper are not designed for the intervention. Furthermore, conducting the study in Mindhelper’s natural use context would preclude the establishment of a control group, thereby making it impossible to evaluate its effects within the framework of an RCT.

A key challenge is expected to be adherence in the intervention group, meaning the extent to which participants in the intervention group engage with Mindhelper. Our feasibility study indicated (very) low engagement when participants were solely provided with a link to Mindhelper by the end of the T1 survey [18]. Therefore, the SMS text message campaign was developed, aiming to boost adherence; however, we do not know yet whether this was sufficient.

Low adherence could lead to misclassification of exposure within the intervention group, potentially introducing bias into results. If nonadherence is unrelated to mental health outcomes (nondifferential misclassification), this misclassification could reduce observed intervention effects. However, if nonadherence is related to mental health outcomes (differential misclassification), this could either inflate or attenuate the observed effect, depending on adherence patterns. We will conduct sensitivity analyses based on the as-treated principle (complier average causal effect) to assess potential effects under full adherence. Adherence data will be collected in binary format (yes or no) at T2 to T4 for the intervention group. For the control group, adherence will be assessed at T1 and T4. In the feasibility study, participants’ self-reports on specific Mindhelper features used did not align with their actual web history [18]. Therefore, we have revised our approach, asking the intervention group to describe how they have used Mindhelper and Ro apps in open-text questions, which will be coded with natural language processing models. Furthermore, qualitative information will provide insights into participant engagement and reasons for nonuse, and aggregated data on participants’ interaction with the SMS text message campaign will provide information on adherence.

It must be noted that the self-guided nature of Mindhelper and the diversity of topics covered mean that adherent participants in the intervention group may engage with different content and receive varying “doses” of the intervention, which aligns with the real-world application but makes the evaluation more complex.

Low retention rates are a major challenge in digital mental health trials [55]. In particular, for self-guided services, the average level of dropout from treatment for depression has been found to be 26%, while for guided services, it has been found to be 72% [56]. Retention proportion will be regularly reviewed to evaluate whether the assumption regarding retention in the sample size calculation is correct or whether the number of participants included should be revised to secure the statistical power of the primary analysis. Missing data will further be addressed through multiple imputations. If we retain a response proportion of 64% at T2 (primary end point), as was the case in the test phase of this study, this may not be as critical as in other studies of self-guided digital services. However, nonrandom dropout could still introduce bias into the findings, potentially skewing the results and overestimating or underestimating the true impact of Mindhelper, depending on the characteristics of those who drop out compared to those who remain in the study.

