**Figure 1 figure1:**
[figure not shown]
Overview of the study design.

Participants are randomized upon responding to the baseline (T1) survey, and based on their group assignment, they will receive information about Mindhelper at the end of the survey (intervention group) or be informed that they have been placed in the control group. All data are collected online (in SurveyXact [Ramboll Management Consulting]). Randomization is conducted automatically in the survey setup and is done independently of the participants’ responses at T1. There is no care provider or outcome assessor, as all measures are self-reported and collected through online questionnaires. Randomization, invitations for follow-ups, reminders to nonresponders, and distribution of information to the intervention group were all done automatically and independently of the research team.

By the end of the T1 survey, participants are asked to provide their mobile numbers, and invitations to follow-up surveys are sent by SMS text messages. Therefore, it is solely participants completing the T1 survey who can be invited to the follow-up surveys. In our feasibility study, participants preferred being contacted via SMS text messages as compared to emails, which is consistent with studies exploring how to engage young people in digital mental health interventions [18,30].

All participants aged between 15 and 25 years who complete the T1 survey will be invited to respond to follow-up surveys 2 weeks after randomization (T2), 6 weeks after randomization (T3), and 12 weeks after randomization (T4). By the end of the survey at T4, the control group will be informed about Mindhelper and directed to the website.

Our feasibility study revealed very low engagement when participants were merely provided with a link to Mindhelper at the end of the T1 survey [18]. To increase use in the intervention group, we developed an SMS text message campaign. Participants will receive 29 SMS text messages throughout the study, each offering tips and guidance on using Mindhelper. Each SMS text message links to a restricted section of the website, where participants are introduced to a specific theme or feature through brief texts and videos before being guided to the unrestricted section of the website. Multimedia Appendix 1 provides a detailed overview of the campaign themes.

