The recruitment strategy will be monitored weekly throughout the study period and adjusted to target individuals underrepresented in the sample based on these characteristics. The ability to create multiple advertisements targeting different populations, closely monitor their real-time performance, and continuously adjust them makes online advertising a powerful tool for recruiting according to specific demographic requirements. However, as of November 6, 2023, Meta Platforms, Inc has prohibited direct advertisement to individuals aged <18 years due to European Union legislation. This regulatory change may challenge our goal of achieving equal representation across age groups, yet it remains our target.

In the feasibility study, we neither defined an optimal study population composition nor adjusted the recruitment strategy, resulting in a sample with 87.3% (488/559) women [18]. To increase male participation, we will include Reddit as a recruitment platform in this study. As of 2024, 63.6% of Reddit’s global users were male individuals [31], compared to 52% on Instagram [32] and 57% on Facebook [33]. In Denmark, 41% of Instagram users and 46% of Facebook users are male individuals [34]. While Danish user demographics for Reddit are unavailable, we assume they align with global trends.

Figure 2 illustrates the recruitment process, from viewing an advertisement on one of the platforms to becoming a study participant. From the advertisements, young people will be directed to a landing page containing information about the study design, data protection, and other details, presented with graphics and a short explainer video [35]. If they choose to participate, they will be guided to the T1 survey and provided with additional information before they provide consent to participate. The participants are informed that the study is conducted in collaboration between the region of Southern Denmark and the National Institute of Public Health, University of Southern Denmark.

At the end of the T1 survey, the intervention group will receive information about Mindhelper and will be automatically directed to Mindhelper [20], while the control group will not receive any information about Mindhelper but instead receive instructions about the next steps in the study. website

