**Use of Mindhelper**					
	Digital behavior when feeling down	✓	✓	✓	✓
	Use of Mindhelper (in the intervention group)		✓	✓	✓
	Thoughts on the SMS text message campaign (in the intervention group)		✓	✓	✓
	Familiarity with or use of Mindhelper and Ro (at T1 for all participants and at T4 for the control group)	✓			✓

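### The complier analysis is described as as-treated and as giving effects under full adherence, but the method specified estimates the effect of any reported use among those who used because of assignment

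*Protocol article*

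**What the plan says.** Two places in the protocol article describe the same analysis.

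- **Planned Statistical Analysis, Overview.** The complier average causal effect is estimated by the contamination-adjusted intention-to-treat method. The article presents this as an instrumental-variable approach that keeps the benefits of randomization. The adherence measure is self-reported Mindhelper use at T4 in both arms.
- **Discussion, Conclusions.** The article plans sensitivity analyses that it calls as-treated, with the complier average causal effect named in brackets. It gives their purpose and the measure as: "to assess potential effects under full adherence. Adherence data will be collected in binary format (yes or no) at T2 to T4". That schedule is for the intervention arm. The schedule in controls is different: "For the control group, adherence will be assessed at T1 and T4". The same section concedes that adherent participants "may engage with different content and receive varying" doses of the intervention.

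What assignment delivers is set out elsewhere. Under Recruitment, once T1 is finished: "the intervention group will receive information about Mindhelper and will be automatically directed to Mindhelper". Under Study Design, the intervention group gets 29 text messages with links to access-restricted web pages: "where participants are introduced to a specific theme or feature through brief texts and videos before being guided to the unrestricted section". The Conclusions section says that the trial evaluates the combined effect of the campaign and Mindhelper.

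**The concern.** An as-treated analysis compares reported users with reported non-users whatever their allocation, and so gives up the randomized comparison. An instrumental-variable analysis keeps it. One analysis cannot be both.

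Full adherence is never defined. A yes/no use variable with conceded variation in dose cannot represent it. Reading the complier effect as the effect if everyone adhered fully needs two further assumptions that the article does not make: that those who did not take up the service would have responded as the compliers did, and that any reported use amounts to full use.

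The method also needs assignment to act on the outcome only through reported use. Here assignment brings a redirect, messages and campaign pages as well. If these do anything for people who answer no, the analysis attributes it to those who answer yes.

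At stake is interpretation. When uptake is low the complier estimate can be several times the trial effect, and a reader told that it shows full adherence would take it as what the service delivers when properly used.

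**Working it through.** **The plan's own figure.** The Sample Size Calculation gives an effect size of 0.1 and an SD of 19.4, so the target difference is 0.1 × 19.4 = 1.94 WHO-5 points. A two-sided 5% t-test with 80% power needs 1570.7 per arm, rounded up to 1571, or 3142 in total. This matches the article and is not at issue. The article gives no figure for the complier analysis.

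**What the method estimates.** Let p1 and p0 be the proportions reporting use in the intervention and control arms. Assume that assignment discourages nobody from use. Participants then fall into three groups:

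- those who report use either way: p0
- those who report use because of assignment: p1 - p0
- those who report no use either way: 1 - p1

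Let C be the effect in the middle group, and d the effect of assignment (redirect, messages) in the last group. Take the effect of assignment in the first group as zero. Then:

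- intention-to-treat effect = (p1 - p0) × C + (1 - p1) × d
- instrumental-variable estimate = intention-to-treat effect / (p1 - p0) = C + d(1 - p1)/(p1 - p0)

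With d = 0 the estimate is C: an average over whatever doses the middle group took. Neither a full-dose effect nor the effect in the other two groups enters it. With d above zero the estimate is too high by the second term; with d below zero it is too low.

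**Illustration.** The intention-to-treat effect is set at 1.94, the planned T2 difference, used here only as a scale. The values of p1, p0 and d are assumptions; the article gives none of them. Each cell shows C = (1.94 - (1 - p1) × d)/(p1 - p0). The d = 0 column is what the method would report.

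| p1 | p0 | d = 0 | d = 0.5 | d = 1.0 |
|---|---|---|---|---|
| 0.20 | 0.02 | 10.78 | 8.56 | 6.33 |
| 0.50 | 0.02 | 4.04 | 3.52 | 3.00 |
| 0.90 | 0.05 | 2.28 | 2.22 | 2.16 |

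First row, d = 0.5: the shift is 0.5 × 0.80/0.18 = 2.22, and 10.78 - 2.22 = 8.56. Second row: 0.5 × 0.50/0.48 = 0.52. Third row: 0.5 × 0.10/0.85 = 0.06.

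The possible shift is therefore large only if reported use is low. The Conclusions section reports very low engagement in the feasibility study, when only a link was given, and says that it is not yet known whether the messages were sufficient.

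**The case against.** The defence has several fair points. The operative definition in the analysis overview is a sound, named method. The sentence in the Discussion itself names the complier average causal effect and says potential effects. Varying doses, weak self-report on features used and the combined nature of the intervention are all disclosed. The restricted campaign pages are on the website, so someone who read them may well report use, and the messages are described as guidance on using Mindhelper. The direct effect d could be close to zero. Misreporting adds uncertainty in either direction: over-reporting in the intervention arm, for example, would enlarge the denominator and shrink the estimate.

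All of this limits the size of the problem. It does not make the Discussion's description of the target correct.

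Three stronger readings are tempting and are not supported:

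- **The redirect makes nearly everyone a user, so the exposure is meaningless.** This depends on how the use item is worded and coded, which the article does not show and may leave to the questionnaire or the published analysis plan.
- **The arms are measured differently.** Table 1 lists "Use of Mindhelper (in the intervention group") and a separate familiarity-or-use row for controls at T4. But the analysis overview says that use is the measure in both arms, and a table row condenses a questionnaire.
- **The estimate is wrong by some fixed multiple.** Dividing 1.94 by different assumed uptakes gives very different figures, but different definitions of use are different target quantities. The spread does not show an error.

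**Conclusion.** The point stands as an error of description plus an unstated assumption. The Discussion claims a property, the effect under full adherence, that the specified analysis does not have, and it names a different method. The estimate is the effect of any reported use, of campaign and Mindhelper together, among those who used because of assignment.

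The no-direct-effect assumption is open to doubt on the article's own account of what assignment delivers. The shift, d(1 - p1)/(p1 - p0), is upward if d is positive, but neither d nor the use rates can be taken from the article. In the table it runs from 0.06 to 4.44 points, all under assumed inputs.

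Only a sensitivity analysis is affected. The primary intention-to-treat analysis is unchanged.

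**What to change.** 1. In the Discussion, delete the reference to the as-treated principle. Replace the full-adherence phrase with: *the effect of any reported use (of the campaign and Mindhelper combined) among participants who used because of assignment*. Use the same description when results are reported.
2. State the assumption that assignment has no effect in participants who report no use.
3. Rerun the same model over a small range of d, including d = 0. In practice, subtract d from the outcome of intervention-arm participants who report no use, within each imputed data set, and refit. This reproduces the formula above.
4. Apply one criterion, use and not familiarity, in both arms.

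Redefining exposure as contact after the T1 redirect is not advised. It would leave the redirect as a route from assignment to outcome outside the exposure. It would also need individual contact data: the article says that individual use metrics are not collected and that interaction with the messages is recorded only in aggregate. Nothing in the article shows that the survey items on thoughts about the campaign record page visits.

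The cost is a wording change and one additional run over the values of d. The downside is that a range is reported beside the single figure.
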